## Abstract

**Background:**

Social isolation and loneliness (SIL) worsens mortality and other outcomes among older adults as much as smoking. We previously tested the impact of the HOW R U? intervention using peer support from similar-aged volunteers and demonstrated reduced SIL among older adults discharged from the emergency department (ED). Generativity, defined as “the interest in establishing and guiding the next generation,” can provide an alternative theoretical basis for reducing SIL via intergenerational programs between members of younger and older generations. The current protocol will examine the impact of younger intergenerational volunteers providing the HOW RU? intervention.

**Methods:**

In this randomized clinical trial, we will compare the following three arms: (1) the standard same-generation peer support HOW R U? intervention, (2) HOW R U? intervention delivered by intergenerational volunteers, and (3) a common wait-list control group. Outcome assessors will be blinded to the intervention. Trained volunteers will deliver 12 weekly telephone support calls. We will recruit participants ≥ 70 years of age with baseline loneliness (six-item De Jong loneliness score of 2 or greater) from two EDs. Research staff will assess SIL, depression, quality of life, functional status, generativity, and perceived benefit at baseline, at 12 weeks, and 24 weeks post-intervention.

**Discussion:**

We hypothesize participants receiving the intergenerational intervention will show improved outcomes compared to the control group and peer support HOW R U? intervention. We also hypothesize that participants with higher perceptions of generativity will have greater reductions in SIL than their lower generativity counterparts. Aging is experienced diversely, and social interventions combatting associated SIL should reflect that diversity. As part of a program of research following the Obesity-Related Behavioral Intervention Trials (ORBIT) model, the findings of this RCT will be used to define which intervention characteristics are most effective in reducing SIL.

**Trial registration:**

ClinicalTrials.gov NCT05998343 Protocol ID:21-0074E. Registered on 24 July 2023.

## Background

Older adults use emergency services at higher rates and also are more likely to experience social isolation and loneliness (SIL) than younger people [1]. Socially isolated and lonely older adults have an increased risk of all-cause mortality rivaling that of risk factors such as obesity and smoking, as well as an increased rate of admission to long-term care and unplanned emergency hospitalization [2–4]. Facing an aging population, preventative measures to address this important public health issue are needed, and the emergency department (ED) is a novel setting to identify SIL and to intervene [5, 6]. Lowthian et al. conducted a pilot trial of a support program called “HOW R U?” for older adults after discharge from the ED which showed reduced symptoms of depression and SIL from baseline among older adults [4]. Our research group is currently conducting a three-arm RCT comparing the same-generation peer support “HOW R U?” intervention delivered by telephone or video call to a common control group (clinicaltrials.gov # NCT05228782). The theoretical framework for the original HOW R U? intervention was based on “peer support”—the “provision of knowledge, experience, emotional or practical help by someone sharing common characteristics”—which facilitates the sharing of common experiences and empathetic communication [4, 5].

A review of interventions for SIL found that those based on a theoretical framework, such as the theory of generativity, are more likely to improve outcomes [7]. Further, Fakoya et al. highlighted that “there is no one-size-fits-all approach to loneliness interventions” [8]. Thus, there is a need to assess the effectiveness of different types of interventions to meet differing experiences of loneliness.

Compared to peer support interventions from similar-aged volunteers, “intergenerational” interventions pair members of younger and older generations with a focus on mutual benefit [9]. These intergenerational interventions are based on Erikson’s theory which posits that generativity, defined as “the interest in establishing and guiding the next generation”, is an important need that remains so into older adulthood (see Appendix 1 for further details of this theoretical framework) [10]. Evidence suggests this may produce reciprocal benefits for the client and volunteers including improved productivity, increased social interaction, enhanced self-perceptions of generativity, and feelings of self-worth among its participants [7, 8]. In addition, recent research suggests that generativity may in itself be a modifiable construct potentially yielding benefits in mental and physical well-being [10].

The current protocol is part of a program of research following the Obesity-Related Behavioral Interventional Trials (ORBIT) model whereby complex behavioral interventions are systematically refined to prevent premature evaluation, similar to the development of pharmaceuticals [11].

### Study purpose

Our primary outcomes are to assess whether the intergenerational HOW R U? intervention (1) reduces SIL more than the waitlist control group at study week 12 and (2) reduces SIL more than the current same-generation peer support HOW R U? intervention at study week 12.

Secondary outcomes include assessing:The impact of the intergenerational HOW R U? intervention on (i) SIL at study week 24, (ii) depression, (iii) quality of life, (iv) functional status, (v) generativity, (vi) participant’s perceived self-benefit, and (vii) participant’s perceived benefit for the volunteer delivering the HOW R U? intervention at study weeks 12 and 24.Participant stated preferences for intergenerational versus same-generation peer support HOW R U? intervention prior to randomization. Note, participants will be randomized regardless of their intervention preference.

## Methods/design

This protocol describing a three-arm RCT was developed following SPIRIT guidelines for reporting trial protocol and a SPIRIT guidelines checklist is attached [12]. Per SPIRIT guidelines, trial registration information is summarized in Tables 1 and 2.

**Table 1 Tab1:** SPIRIT schematic diagram of enrolment, interventions, and assessments. Listed assessments are completed for all intervention groups

	**Enrolment**	**Allocation**	**Post-allocation**		
Timepoint	***Pre-intervention***	**Time 0**	***Intervention (12 weeks)***	***12 weeks’ follow up***	***24 weeks’ follow up***
Enrolment:					
Eligibility screen	X				
Informed consent	X				
Allocation		X			
Interventions:					
* Intergenerational intervention*			X		
* Peer-support intervention*			X		
* Waitlist control*					
Assessments:					
* Demographic data*	X			X	X
* De Jong Loneliness Scale*	X			X	X
* Lubben’s Social Network Scale*	X			X	X
* Geriatric Depression Scale*	X			X	X
* Brief Alzheimer’s Screening Test*	X			X	X
* EQ-5D-5L*	X			X	X
* Older Americans Resources Scale*	X			X	X
* Loyola Generativity Scale*	X			X	X
* Perceived benefit by the participant*	X			X	X
* Volunteer benefit perceived by participant*	X			X	X

**Table 2 Tab2:** World Health Organization Trial Registration Data Set

Data Category	Information
Primary registry and trial identifying number	Clinicaltrials.gov NCT05998343
Date of registration in primary registry	24 July, 2023
Secondary identifying numbers	Protocol ID:21-0074E
Source(s) of monetary or material support	N/A
Primary sponsor	N/A
Secondary sponsor(s)	N/A
Contact for public queries	[name] [contact]
Contact for scientific queries	[name] [contact]
Public title	Intergenerational Program for Social Isolation and Loneliness in Older Adults Discharged From the Emergency Department
Scientific title	Impact of an intergenerational program to improve loneliness and social isolation in older adults initiated at the time of emergency department discharge: Study protocol for a three-arm randomized controlled trial
Countries of recruitment	Canada
Health condition(s) or problem(s) studied	Social isolation, loneliness
Intervention(s)	1. HOW R U? intervention delivered by same-generation peer volunteer 2. HOW R U? intervention delivered by intergenerational volunteer 3. No intervention
Key inclusion and exclusion criteria	Inclusion Criteria 1. Community-dwelling person 70 years of age and older receiving care from the ED, Family Medicine or Geriatric clinics at the two participating sites (MSH, NYGH) 2. Baseline de Jong loneliness score of 2.0 will be required for participating in the trial Exclusion Criteria 1. Age less than 70 years of age 2. Patients with communication problems (critically ill, unconscious, language barrier, speech impairment or otherwise unable to provide consent) or admission to a hospital for greater than 72 h) 3. Patients with severe cognitive impairment or those with living in nursing homes who are dependent on others for their activities of daily living 4. Patients without any mobile phone or landline Volunteer Inclusion Criteria 1. Peer-support volunteers will be 60 years of age or older 2. Intergenerational volunteers will be between 19–39 years of age
Study type	Interventional Allocation: Randomized interventional model. Parallel assignment. Outcome assessor masking Primary purpose: Supportive Care
Date of first enrolment	November 1, 2021
Target sample size	141
Recruitment status	Recruiting
Primary outcome(s)	1. Change in loneliness using De Jong Gierveld 6-item Loneliness Scale from baseline to 12 weeks
Key secondary outcomes	1. Change in loneliness using De Jong Gierveld 6-item Loneliness Scale from baseline to 24 weeks 2. Change in perceived social support using Lubben Social Network Scale from baseline to 12 and 24 weeks 3. Change in mood using Geriatric Depression Scale from baseline to 12 and 24 weeks 4. Change in baseline cognition using “Brief Alzheimer’s Screening Test” from baseline to 12 and 24 weeks 5. Change in Quality of Life using Euro-Qual 5 Dimensions 5 Levels from baseline to 12 and 24 weeks 6. Change in Functional Status using Older Americans Resource Scale from baseline to 12 and 24 weeks 7. Change in self-perceptions of generativity using Loyola Generativity Scale from baseline to 12 and 24 weeks 8. Perceived benefit to participant at 12 and 24 weeks 9. Perceived benefit to volunteer at 12 and 24 weeks

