### Hypotheses

Our primary hypothesis is that participants who receive the intergenerational HOW R U? intervention will have superior outcomes compared to the waitlist control group and to the same-generation peer support HOW R U? intervention. Our second hypothesis is that participants with higher perceptions of generativity will have greater reductions in SIL. Third, we hypothesize that participants in the intergenerational intervention will have higher perceptions of generativity after 12 weeks than the same-generation peer support and waitlist control groups.

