### Data collection

Research assistants will collect data for all groups over the telephone. Initial screening of potential participants by research staff involves the six-item De Jong loneliness scale which is described in further detail below. We will then collect demographic data including age, gender, living arrangement, pet ownership, educational attainment, technology profile index (modified), and baseline assessments of primary and secondary outcomes (see the “Outcome measures” section) from eligible participants who provide informed consent. Trained research staff will obtain verbal informed consent for this study as approved by all participating institutional REBs (see Appendix 2 for the informed consent model). Research staff are not involved in the clinical management of participants to avoid the perception of coercion. In order to allocate patients to specific arms, a statistician independent of the trial management will use a computer procedure to generate a variable block randomization list with blocks varying between four and eight. Note, as in our previous trial, research staff involved in outcome assessment will be blinded to randomization status. After completion of the 12-week intervention, research assistants will reassess outcomes within 2 weeks (study week 12–14) and 12 weeks (study week 24). To minimize the potential Hawthorne Effect, study endpoints will be collected only upon completion of the intervention [17]. Personal health information is removed from all study databases. Deidentified data will be stored in a password-protected computer accessible only by the study’s research assistants and corresponding author and will remain confidential. As this is a minimal-risk study, no formal data monitoring committee was required by our REB. A study committee consisting of the principal investigator, coauthors, and statistician will have regular meetings once a quarter to discuss ongoing data collection, quality, and outcomes. Note, no interim analyses are planned in this minimal-risk study.

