### Outcome measures

The primary outcome is loneliness as measured using the six-item De Jong loneliness scale after completion of the intervention (weeks 12–14 of the study). The De Jong scale has been extensively validated in older populations and is divided into four clinically relevant categories: 6—severe loneliness, 4–5—moderate-to-severe loneliness, 2–3—low loneliness, and 0–1—no loneliness [12].

The secondary outcomes are the following: (1) the de Jong loneliness Scale at 12 weeks post-completion of the intervention to assess sustainability (study week 24); (2) six-item Lubben’s Social Network Scale [18]; (3) five-item Geriatric Depression Scale to assess mood [19]; (4) Brief Alzheimer’s Screening Test to assess baseline cognitive performance [20]; (5) EQ-5D-5L to assess perceived health-related quality of life in the areas of self-care, mobility, usual activities, pain/discomfort, and anxiety/depression [21]; (6) the Older Americans Resource Scale to assess functional status [22]; (7) the Loyola Generativity Scale to assess generativity [23]; (8) perceived benefit by the participant; and (9) benefit to the volunteer as perceived by the participant. The standardized measurement instruments selected for the trial have been extensively validated in older adults. The Loyola Generativity Scale has demonstrated good interrater reliability as well as responsiveness in trials of older adults [24, 25]. To assess the secondary outcome of participant preference for same-generation peer support versus intergenerational HOW R U? intervention, we will use a 5-point Likert scale with the following options: “I strongly prefer peer support,” “I prefer peer support,” “neutral,” “I prefer intergenerational,” and “I strongly prefer intergenerational”. Please see Appendix 3 for full details.

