### Sample size and power

Each group will consist of a sample of 47 subjects which will detect a 13.9–28.1% difference between the treatment and control groups in the proportion of people who improve by one category (e.g., from severe loneliness to moderate-to-severe loneliness) with a power greater than 80%. This assumes that up to 15% of control group participants may have a spontaneous improvement in loneliness categories. With these sample sizes, three comparisons may be made: intergenerational intervention to the control group, same-generation peer support intervention to the control group, and intergenerational to the same-generation peer support intervention.

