### Analysis

All analyses will use SAS Version 9.4 (SAS Institute, Cary, NC, USA). A two-sample two-sided test of proportions will be used to assess the primary outcome of loneliness in the control group versus the intergenerational HOW R U?, and the control group versus the same-generation peer support HOW R U? intervention. Improvements in the binary outcome of the loneliness category of the De Jong Loneliness Scale will be assessed using a logistic regression model, and results will be reported as odds ratios with the corresponding 95% confidence intervals. The variance inflation factor (VIF) will be calculated to assess for multicollinearity before the logistic regression model is built such that if two variables are highly correlated (i.e., VIF > 4 or tolerance < 0.25), only one of the two variables is retained for the final model. To compare the secondary outcomes, they will be reported as means with corresponding 95% confidence intervals.

Potential missing data will be managed as follows. For logistic regression, participants with more than 15% missing data for confounding variables will be excluded from the analysis. Note that in the main trial, less than 5% of participants would have been excluded. For participants with less than 15% missing data, we will use imputation for confounding variables. Participants with missing outcome data will be excluded from analysis (i.e., lost to follow-up). Note that after two-thirds of the participants have been enrolled, we will assess the loss-to-follow-up rate and adjust the enrollment accordingly. For example, if the lost-to-follow-up rate is 20%, we will increase the enrolment by 20%. To manage protocol nonadherence, participants will be analyzed using intention-to-treat analysis regardless of their adherence to the protocol.

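### Generativity hypothesis 3 is worded as a week-12 level but registered as change from baseline, and the stated comparison of means makes no use of the baseline score

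*Protocol article*

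**What the plan says.** Four places in the protocol article bear on the generativity outcome.

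- **Hypotheses.** The third hypothesis is that intergenerational participants "will have higher perceptions of generativity after 12 weeks than the same-generation peer support and waitlist control groups". Read plainly, this compares levels at week 12.
- **Table 2, key secondary outcomes.** The registered form is "Change in self-perceptions of generativity using Loyola Generativity Scale from baseline to 12 and 24 weeks". The other scales are worded the same way, for example "Change in mood using Geriatric Depression Scale from baseline to 12 and 24 weeks". Only the two perceived-benefit items are not changes.
- **Outcome measures.** The list says only "the Loyola Generativity Scale to assess generativity" and chooses neither form.
- **Analysis.** The one sentence on secondary outcomes is "To compare the secondary outcomes, they will be reported as means with corresponding 95% confidence intervals". It names neither level nor change and mentions no covariate. The only regression in that section is the logistic model for the loneliness category.

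A baseline value will exist. Data collection includes "baseline assessments of primary and secondary outcomes", and Table 1 marks the generativity scale before the intervention and at both follow-ups, in all arms.

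**The concern.** Hypothesis 3 tests the mechanism that motivates the intergenerational arm, and the Discussion concedes uncertainty about whether the intervention can raise generativity. With two raw forms named and neither tied to the analysis, the form could be chosen after the results are known, and in a trial of this size the two can point different ways. Both raw forms also leave unused some of the information in a baseline score that is collected anyway. The same loss of precision applies to the other scale outcomes if they are compared as raw means.

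**Working it through.** **Inputs.** "Each group will consist of a sample of 47 subjects" (Sample size and power). The protocol states no significance level; I assume two-sided 5%, in line with its 95% intervals and its two-sided primary test. It gives no SD, target difference or baseline to week-12 correlation r for generativity. Results are therefore in SD units, r runs over an assumed range, and the SD is assumed equal at both visits.

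**The plan's own figure.** The 47 per group is set for the binary primary outcome. Comparing 15% with 15% + 28.1% = 43.1%, at two-sided 5% and 80% power with continuity correction, gives 47. The lower end of the stated range does not follow from the same formula (0% against 13.9% gives 65). Neither bears on this point, and there is no generativity figure to reproduce.

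**Step 1: how far the two forms can differ.** Let L be the between-arm difference in week-12 means, C the difference in mean change, and D the difference in baseline means. Then C = L − D. D has mean zero under randomization and standard error √(2/47) = 0.206 SD, so its 95% range is ±1.96 × 0.206 = ±0.40 SD.

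**Step 2: unbiased overall, shifted given an imbalance.** With true difference δ, the expectation given D is δ + rD for L and δ − (1 − r)D for C. Averaged over randomizations, both equal δ. Given D = 0.40 SD and r = 0.5, the level is shifted by +0.20 SD and the change by −0.20 SD. A baseline-adjusted comparison removes both shifts.

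**Step 3: precision.** In units of 2·SD²/n, the variance is 1 for level, 2(1 − r) for change and 1 − r² for the adjusted comparison (ANCOVA), ignoring the small cost of estimating one slope. The extra participants needed to match the adjusted analysis are the ratio to 1 − r², less 1; for r = 0.7, 1/0.51 = 1.96 and 0.60/0.51 = 1.18. The detectable difference at 80% power is (1.960 + 0.842) × 0.206 × √variance.

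| r | Variance: level / change / adjusted | Extra participants: level / change | Detectable difference (SD): level / change / adjusted | Power for 0.5 SD (%): level / change / adjusted |
|---|---|---|---|---|
| 0.3 | 1.00 / 1.40 / 0.91 | 10% / 54% | 0.58 / 0.68 / 0.55 | 67.9 / 53.5 / 71.9 |
| 0.5 | 1.00 / 1.00 / 0.75 | 33% / 33% | 0.58 / 0.58 / 0.50 | 67.9 / 67.9 / 79.9 |
| 0.7 | 1.00 / 0.60 / 0.51 | 96% / 18% | 0.58 / 0.45 / 0.41 | 67.9 / 87.9 / 92.4 |
| 0.8 | 1.00 / 0.40 / 0.36 | 178% / 11% | 0.58 / 0.37 / 0.35 | 67.9 / 96.9 / 98.1 |

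**Step 4: how often the verdicts differ.** In a simulation of 1,000,000 trials for each r from 0.3 to 0.9, the level and change tests disagreed on significance in 7.5% to 9.2% of trials with no effect, and in 29.5% to 32.1% with a true 0.5 SD effect.

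**The case against.** The best defence is that nothing here is a contradiction in substance. The hypothesis is one directional sentence and Table 2 is a registry summary with short titles. Under randomization both forms estimate the same difference. This stands: a reader might infer two rival treatment effects, or a biased analysis, and the documents support neither. The shifts in Step 2 are conditional on a chance imbalance and add variance, not systematic error.

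A reader might also infer that the registered change wording rules out adjustment. It does not: regressing change on arm and baseline gives the same treatment effect as regressing the week-12 score on arm and baseline. Nor does the Analysis sentence forbid a covariate, and an analysis plan that is not shown may name one. That limits the weight of the point but does not remove it. The protocol makes two differently worded statements of one outcome and states a method of comparison that does not use the baseline; naming the adjusted comparison improves on that method at no cost.

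The size is easy to overstate. A third more participants applies at r = 0.5, the value at which the better of the two raw forms loses most. Against the registered change form, the loss is 18% at r = 0.7 and 11% at r = 0.8. Equal SDs are assumed and have not been shown for every scale, for instance the depression score that runs from 0 to 5. Finally, the protocol gives no rule for declaring hypothesis 3 supported, so a reversed formal decision cannot be claimed.

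**Conclusion.** The point holds as a modest one about secondary outcomes. The wording of hypothesis 3 and its registered outcome differ, and the stated comparison of means settles neither the form nor the use of the baseline. The two raw forms target the same effect but differ by an imbalance with standard error about 0.21 SD at 47 per arm. With equal SDs, both are less precise than the adjusted comparison for every r strictly between 0 and 1. How much less depends on r and on which raw form is used, so the range in the table should be quoted and not a single figure. The absolute figures also assume 47 analysed per arm; the relative ones do not depend on that number.

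**What to change.** In the Analysis section, state that the scale outcomes at weeks 12 and 24 are compared between arms as adjusted mean differences with 95% confidence intervals, with the scale's own baseline score as covariate. The response may be the visit score or the change. Name the adjusted week-12 difference in generativity as the single estimate for hypothesis 3, and align the Hypotheses section and Table 2 with it. Keep raw mean changes as description.

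The cost is wording in the protocol, analysis plan and registry entry. No data, visits or participants are added. The change should be made and dated before any comparison by arm is seen.
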